## Limitations

4

This study will have several limitations. First, the trial will be designed to directly reflect the real-world performance of each analgesic strategy and therefore will not incorporate placebo controls. The fundamental differences among the interventions necessitate an open-label design, which may introduce potential biases in subjective outcomes, such as detection bias and reporting bias. Second, this will be a single-center clinical trial with a relatively small sample size, which may limit the generalizability of the findings. Larger, multicenter studies will be needed to validate these results. Third, the implementation of strict inclusion and exclusion criteria will exclude certain patient subgroups, which may further restrict the applicability of our findings to broader populations. Future research will need to focus on evaluating the safety and efficacy of this strategy in more diverse and representative patient cohorts.

## Conclusion

5

This randomized controlled trial aims to provide rigorous evidence regarding the efficacy and safety of a single-injection thoracic paravertebral block using liposomal bupivacaine for post-thoracotomy analgesia. The study will specifically evaluate the quality of analgesia provided by this catheter- and opioid-free strategy in specific patient populations. Additionally, we will observe its impact on other postoperative recovery indicators and the incidence of adverse effects such as PONV. Our findings are expected to facilitate broader clinical adoption of this approach, thereby enhancing postoperative recovery outcomes. Future research should continue to explore the long-term benefits and broader applicability of this strategy across different surgical populations.

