### Safety outcomes

2.6

Safety outcomes will include the adverse events related to regional nerve blockade, such as allergic reactions, total spinal anesthesia, severe hypotension, malignant arrhythmias, and cardiac arrest, as well as postoperative complications including urinary retention, puncture site infection, pulmonary infection, deep vein thrombosis, pulmonary embolism, and atelectasis. All adverse events will be recorded and assessed throughout the study period.

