### Randomization and blinding

2.7

This open-label, three-arm randomized trial will assign 162 participants in a 1:1:1 ratio (Group L, Group R, and Group P, with 54 participants per group). An open-label design will be adopted due to fundamental differences in postoperative pain management protocols among the three groups. To facilitate protocol-adherent adjustments in analgesia, both investigators and participants will not be blinded to treatment allocation. Nevertheless, postoperative outcome assessments will be performed by trained nurses who are not involved in the intervention procedures to minimize potential bias.

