### Statistical analysis

2.11

The normality of continuous variables will be assessed using the Shapiro–Wilk test. Data following a normal distribution will be reported as mean (standard deviation, SD), while non-normally distributed data will be presented as median (interquartile range, IQR). Binomial variables will be expressed as proportions. The correlation structure will be selected based on the quasi-likelihood under the independence model criterion (QIC). Data distribution will determine the use of either a normal or gamma distribution with identity or log-link functions. The primary hypothesis of this study is that group L can demonstrate a superior quality of postoperative recovery compared to both control groups, with the difference being both statistically and clinically significant. A generalized estimating equation (GEE) model will be used to analyze repeated measures of continuous variables accounting for within-subject correlations. Continuous variables measured at a single time point will be analyzed using *t*-tests or Mann–Whitney U tests depending on normality and categorical data will be analyzed using the χ^2^ test. Post-hoc pairwise comparisons are strictly contingent on a significant overall between-group difference and *p*-values are adjusted using the Bonferroni method and set at 0.017. For longitudinal outcomes, this correction governs testing at both the individual time-point and overall treatment effect levels, ensuring robust control of the type I error rate. Statistical significance will be defined as *p* < 0.05.

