All study outcomes will be analyzed in the modified intentiontotreat (mITT) population, including all patients who are randomized, received the assigned intervention, and completed all or part of the postoperative follow-up assessments. Patients will be included in the analysis according to their original allocation. To evaluate the robustness of the primary outcome and its sensitivity to protocol deviations, a per-protocol (PP) analysis will be performed as a sensitivity analysis to verify the reliability of the findings from the intention-to-treat analysis. Multiple testing correction will be applied to primary and secondary outcome measures where applicable. As a theoretical principle, this adjustment is generally not applied to safety indicators. Odds ratios (OR) and corresponding 95% confidence intervals (CI) will be reported where appropriate. No interim analysis will be planned. Missing data will not be imputed. Statistical analyses will be performed using SPSS (version 25.0; IBM SPSS). A two-sided *p*-value < 0.05 will indicate statistical significance, except where false discovery rate (FDR) corrections apply.

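### The conclusion promises rigorous safety evidence, but 54 per arm with a chi-square test and odds ratios cannot supply it for rare events

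*Protocol article*

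**What the plan says.** Section 5 (Conclusion) states that the trial "aims to provide rigorous evidence regarding the efficacy and safety of a single-injection thoracic paravertebral block using liposomal bupivacaine" and links the findings to wider clinical use.

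Section 2.6 (Safety outcomes) lists adverse events of the block, "such as allergic reactions, total spinal anesthesia, severe hypotension, malignant arrhythmias, and cardiac arrest", and postoperative complications that include puncture site infection, pulmonary embolism and atelectasis. No expected rates are given.

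Section 2.7 fixes the arms: "Group L, Group R, and Group P, with 54 participants per group". Section 2.10 derives that number from QoR-15 only. No safety margin, event rate or precision target appears.

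Section 2.11 (Statistical analysis) says that "categorical data will be analyzed using the χ^2^ test" and that "Odds ratios (OR) and corresponding 95% confidence intervals (CI) will be reported where appropriate". On multiplicity it says that "this adjustment is generally not applied to safety indicators", so safety comparisons are in general tested at a two-sided 0.05. The same section plans proportions as the descriptive summary.

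Section 2.8 states that group P receives no nerve block.

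**The concern.** The article makes a claim about safety and also names the tools that are to serve it, and the two do not fit. A superiority-type test on 54 per arm has little power for uncommon harms, so a non-significant result says almost nothing about whether the liposomal bupivacaine block is safe. The odds ratio breaks down where an arm has no events, which is the likely situation for the gravest outcomes listed.

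At stake is how a quiet safety table would be read. The Discussion's favourable safety statement for liposomal bupivacaine concerns local infiltration, so paravertebral safety data from this trial may be given weight. Section 4 admits a small sample, but only as a limit on generalizability.

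**Working it through.** **Inputs.** From the documents: 54 per arm (2.7, 2.10); two-sided alpha 0.05 with safety generally unadjusted, chi-square test and odds ratio (2.11); no block in group P (2.8). Event rates are assumptions, because the documents give none; a range is shown.

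**1. Where 54 comes from.** With n = 2(z₁₋α/₂ + z₁₋β)²σ²/Δ², σ = 12, Δ = 8 and 80% power:

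- alpha 0.05 gives 35.3, so 36;
- alpha 0.05/3 gives 47.1, so 48;
- 48/0.9 = 53.3, so 54.

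The figure reproduces from QoR-15 inputs alone; no safety quantity enters. (This route does not use the intraclass correlation in 2.10, so it does not validate that step, which is a separate matter.)

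**2. Chance of missing a true doubling.** All pairs of event counts (a, b) were enumerated, with a ~ Bin(54, 2p) and b ~ Bin(54, p). Probability was summed where the uncorrected Pearson chi-square gives p < 0.05. The last column is the number per arm needed for 80% power.

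| Control vs group L (assumed) | Power | Missed | n per arm for 80% |
|---|---|---|---|
| 1% vs 2% | 1.4% | 98.6% | 2319 |
| 2% vs 4% | 6.2% | 93.8% | 1141 |
| 5% vs 10% | 15.6% | 84.4% | 435 |
| 10% vs 20% | 30.4% | 69.6% | 199 |
| 20% vs 40% | 62.7% | 37.3% | 82 |
| 30% vs 60% | 88.1% | 11.9% | 42 |

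A tripling from 5% to 15% is missed 58% of the time. A three-arm test with both controls at the lower rate does little better: 84% missed at 5% vs 10%, and 54% at 5% vs 15%.

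**3. Chi-square with few events.** With equal arms, the expected number of events per arm is half the total, so any outcome with fewer than 10 events across two arms has expected counts below 5. For 4 vs 0:

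- χ² = 108 × (4×54)² / (4 × 104 × 54 × 54) = 4.15, p = 0.042;
- Fisher two-sided p = 2 × C(54,4)/C(108,4) = 2 × 316,251/5,359,095 = 0.118.

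The choice of test alone decides significance. For 3 vs 0 the chi-square p is 0.079, so against zero events group L needs 4 events (7.4%) to reach p < 0.05.

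**4. Odds ratio with zero cells.** The probability that at least one of two arms has no events is 1 − [1 − (1−p)⁵⁴]². With the same rate p in both arms, this is 94% at p = 0.5%, 82% at 1% and 56% at 2%. For puncture-related events in L vs P no rate assumption is needed: group P has no puncture, so its cell is zero by design. Where the ratio is estimable it is imprecise. Equal counts of 3 vs 3 give a 95% CI of about 0.19 to 5.2, and 5 vs 5 about 0.27 to 3.7.

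**5. What zero events would show.** The exact two-sided 95% upper limit for 0/54 is 1 − 0.025^(1/54) = 6.6% (5.4% one-sided).

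**6. An interval that survives.** The Newcombe 95% CI for the risk difference is −6.6% to +6.6% for 0/54 vs 0/54. For 5/54 vs 3/54 it is −7.2% to +15.0%, where the chi-square p is 0.46. The interval shows how much harm remains possible; the p-value does not.

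**The case against.** The strongest reply is that this is one phrase in a closing section. The abstract's Discussion claims evidence on efficacy only, and the stated hypothesis is superior recovery. Proportions, recording of all adverse events and reporting of serious events to a monitoring committee are already planned. Section 4 calls for larger multicentre studies. Interval methods are usually left to an analysis plan, and 2.9 mentions one that is not shown. Low power for rare harm is common to efficacy trials of this size.

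Much of this stands. Silence about interval methods would be no finding. But the article is not silent: it names a test and an effect measure that suit sparse outcomes poorly, and it makes a claim that they cannot support. Section 4 defers safety only for more diverse cohorts, not for want of precision.

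Three stronger readings are tempting, and the documents do not support them:

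- A reader might infer that no upper bound on harm is planned. Section 2.11 provides 95% CIs for odds ratios, which have an upper limit whenever they are estimable.
- A reader might infer that a doubling of harm would almost always be missed. That holds only for rare events; the table falls to 37% missed at 20% vs 40% and 12% at 30% vs 60%. Section 2.6 also lists complications whose rates are not given and need not be rare.
- A reader might infer that non-significance will be taken as proof of safety. No section says so.

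**Conclusion.** The point holds in limited form. The claim of rigorous safety evidence goes beyond a design sized on QoR-15 alone, and the named test and effect measure perform badly on sparse or empty cells. At assumed control rates of about 2% or less, a doubling is missed about 94% of the time or more; the miss rate falls as the assumed rate rises. Two results need no assumed rate: the odds ratio for puncture-related events in L vs P is not estimable, and 0/54 leaves rates up to about 6.6% open. All figures take 54 analysed per arm, which is the best case: with 48 the upper limit for zero events is 7.4%. The primary analysis is not affected. The change should be made because it is nearly free and prevents an overclaim about serious harm.

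**What to change.** In 2.11, for the outcomes of 2.6, replace the chi-square test and odds ratio with:

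- the number and percentage with each event per arm, with an exact (Clopper-Pearson) 95% CI;
- risk differences with Newcombe or Miettinen-Nurminen 95% CIs: L vs R for block-related events, and both L vs R and L vs P for postoperative complications. Puncture site infection, which 2.6 lists among the complications, belongs with the L vs R comparisons only;
- a sentence stating that a non-significant difference is not evidence of safety.

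In section 5, claim evidence on efficacy with descriptive safety data, and note that no events in 54 patients excludes only rates above about 6.6%.

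The cost is a few sentences and a few lines of analysis on data already to be collected, with no more patients. The downside is a more modest safety claim and no p-values for safety events.

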## Data Availability

The raw data supporting the conclusions of this article will be made available by the authors, without undue reservation.
